## Registration, screening, enrolment, and randomization

### Registration and screening

Potential participants are all women with PPCM in the first 5 months postpartum displaying clinical signs of heart failure. After explanation of the nature and scope of the study and a sufficient period of reflection, the investigator must obtain the informed consent by means of a standard written statement in non-technical language. Patients may withdraw their consent of participation at any time of the trial without providing a reason. Patients with heart failure symptoms are screened for PPCM by echocardiography and further inclusion and exclusion criteria are evaluated during the enrolment and randomization visit (visit 1).

### Enrolment and randomization (visit 1)

At visit 1, patient eligibility is evaluated based on the inclusion/exclusion criteria (Table 2). If the patient is considered eligible, the medical history is assessed, physical examination, ECG, and echocardiography are performed and the NYHA class and vital signs are documented. The baseline LVEF has to be determined by cardiac magnetic resonance imaging (CMR) within 5 days after beginning of bromocriptine therapy. Alternatively, if the patient does not tolerate CMR or CMR is temporarily not available, it may as an exception be replaced by two separate echocardiograms with determination of the LVEFs (Simpson’s method) by two independent investigators blinded to each others results. Moreover, laboratory tests for NTproBNP, hemoglobin, serum sodium and potassium, glucose, aspartate aminotransferase, alanine aminotransferase, total bilirubin, blood urea, nitrogen, and serum creatinine are measured. The quality of life is assessed by means of a questionnaire.

Patients who are not eligible to participate in the study are asked to provide their demographic (age, parity, ethnic background) and clinical data for the German PPCM registry [5] and the international registry on PPCM, which is part of the ESC EURObservational Research Programme (http://www.eorp.org) [13].

A central computerized randomization (modified according to Pocock 15 and Pocock and Simon 16) of patients fulfilling the inclusion criteria is performed at the Coordination Centre for Clinical Trials at the University of Leipzig (ZKS Leipzig KKS). Patients are randomized in a 1:1 ratio to either the treatment group or the control group. The treatment group receives bromocriptine therapy at a dose of 2.5 mg b.i.d for the first 2 weeks and 2.5 mg o.d. for another 6 weeks (total treatment of 8 weeks with bromocriptine). The control group receives low-dose bromocriptine (2.5 mg o.d.) for up to 1 week to stop lactation. In both groups anticoagulant therapy at a prophylactic dose is administered during the period of bromocriptine treatment to prevent thrombotic side effects of bromocriptine.

Both groups are additionally treated with standard heart failure medication as per current guidelines [14–17]. Specifically, this therapy includes ACE inhibitors or Angiotensin II receptor blockers (ARBs), beta-blockers, mineralocorticoid receptor blockers (MRAs), diuretics, and ivabradine if indicated. In addition, prolactin, NT-pro-BNP, and a set of additional biomarkers for cardiovascular disease, inflammation, and markers specific for the pathophysiology of PPCM will be measured at each visit. Additionally, novel potential biomarkers derived from experimental studies in ongoing PPCM research in our and other labs will be tested for diagnostic accuracy and prognostic value.

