## Eligibility

The inclusion and exclusion criteria are summarized in Table 2. The aim is to enroll patients with newly diagnosed PPCM in accordance to the definition proposed by the Working Group on PPCM from the Heart Failure Association of the European Society of Cardiology (ESC) [1] which is as follows: (a) evidence of heart failure secondary to systolic dysfunction toward the end of pregnancy or in the months following delivery, where no other cause of heart failure is found; (b) it is a diagnosis of exclusion; (c) the left ventricle may not be dilated but the ejection fraction is nearly always reduced below 45 %.

**Table 2 Tab2:** Summarized inclusion and exclusion criteria

Inclusion criteria	Exclusion criteria
Confirmed PPCM according to ESC definition Time-window within 5 months postpartum LVEF ≤35 % At least 18 years of age Ability to give written informed consent	Preexisting cardiac disease (except PPCM with complete resolution) Any preexisting serious conditions Previous cardiac surgery or percutaneous coronary intervention History of alcohol and/or any other drug abuse Contraindication to the planned therapy Concomitant therapy other than specified in the trial protocol Expected low compliance (e.g., by travel distance to trial site) Concomitant participation in other clinical trials

*ESC* European Society of Cardiology, *PPCM* peripartum cardiomyopathy, *LVEF* left ventricular ejection fraction

Specific inclusion criteria include (1) the confirmed diagnosis of new onset PPCM within a time-window of 5 months postpartum; (2) LV ejection fraction (LVEF) below 35 % as assessed by echocardiography; (3) the age of 18 years or older; and (4) the ability to give written informed consent. PPCM is defined as a non-familial form of peripartum heart failure characterized as an “idiopathic cardiomyopathy presenting with heart failure secondary to left ventricular (LV) systolic dysfunction towards the end of pregnancy or in the months following delivery, where no other cause of heart failure is found”.

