## Study objectives

### Primary objectives

The purpose of the study is to evaluate the effect of prolonged blockade of prolactin with bromocriptine on left ventricular function in women with PPCM. The primary endpoint is the change of LVEF from baseline to 6 months follow-up determined at by CMR (Table 3).

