### Statistical consideration

The estimated average change of LVEF during 6 months for the primary endpoint was based on the previous pilot study including 10 patients with and 10 patients without bromocriptine where the average change of LVEF during 6 months was by absolute 23 % higher in the group with bromocriptine [12]. We assume that the average difference between the groups in this study is 12 % absolute, corresponding to a 52 % relative reduction of the effect seen in the pilot study. If we assume that the patients in the control group who receive 1/10 of the cumulative dose given to the patients of the treatment group might have 1/10 of the benefit, this will reduce the average gain in LVEF to 10.8 % in absolute terms with a standard variation of 12 %. Consequently, to detect this difference in a two-sided difference test with a type I error level of 0.05 and a power of 0.9, a total of 54 patients is needed, 27 per group. Therefore, a total of 60 patients (30 per group) should be sufficient to allow for 3 dropouts per group. Regarding the primary endpoint, an analysis of covariance will be performed. The follow-up LVEF will be defined as dependent variable, the treatment group as fixed factor and the baseline LVEF as covariate. As for the secondary endpoints, frequency tables of rates with appropriate 95 % confidence intervals will be performed and comparisons using contingency tables will be compiled. If sufficient numbers of events occur, additional time-to-event analyses, such as Kaplan–Meier estimates of survival curves, will be carried out.

A final detailed plan for the statistical analyses will be developed prior to the end of study and the start of the final analysis.

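### The baseline LVEF may be scanned up to 5 days after bromocriptine starts, so the primary ANCOVA can adjust for a post-treatment value; the likely bias is small and towards no difference

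*Protocol article*

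**What the plan says.** The section on enrolment and randomization (visit 1) sets the timing: "The baseline LVEF has to be determined by cardiac magnetic resonance imaging (CMR) within 5 days after beginning of bromocriptine therapy". If CMR is not tolerated or is temporarily unavailable, two echocardiograms read independently may replace it. No pre-dose timing is stated for that fallback.

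Bromocriptine is what is being allocated: "Patients are randomized in a 1:1 ratio to either the treatment group or the control group". The arms differ from the first day. The rule for the treatment arm, with both durations counted in weeks, reads: "The treatment group receives bromocriptine therapy at a dose of 2.5 mg b.i.d for the first 2 weeks and 2.5 mg o.d. for another 6". For the control arm the rule is: "The control group receives low-dose bromocriptine (2.5 mg o.d.) for up to 1 week to stop lactation". Background therapy runs alongside: "Both groups are additionally treated with standard heart failure medication as per current guidelines".

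The baseline value is used twice. The primary objectives section says "The primary endpoint is the change of LVEF from baseline to 6 months follow-up determined at by CMR". The statistical section specifies an ANCOVA of follow-up LVEF with "the treatment group as fixed factor and the baseline LVEF as covariate".

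An earlier LVEF also exists. The eligibility section requires "LV ejection fraction (LVEF) below 35 % as assessed by echocardiography", and only patients who meet the inclusion criteria are randomised. The document does not name that echocardiographic value as the baseline for the primary analysis.

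**The concern.** A covariate in a randomised comparison should be fixed before treatment can affect it. Here the window opens at the start of the randomised drug and closes 5 days later, with the two arms on different daily doses. If bromocriptine acts within those days, part of its effect is already in the covariate, and the model credits that part to baseline rather than to treatment.

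The discussion section rests the trial's rationale on early blockade of prolactin, so the plan cannot simply take the first days as inert.

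There is a second route. The trial is open-label, so when the scan is done, or whether it is done, could depend on the known allocation. Standard heart failure therapy is running in both arms over the same days, so a systematic difference in scan timing could also separate the baselines. Blinded reading does not correct when a scan took place.

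At stake are a diluted primary estimate and some loss of power in a trial planned on 27 evaluable patients per arm.

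**Working it through.** **Inputs from the protocol article**
- Target difference 10.8 points, SD 12, two-sided alpha 0.05, power 0.9, 27 per group (statistical section).
- Assumed full benefit before the control-arm adjustment: 12 points (same section).
- Daily doses and durations as quoted from visit 1.

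**Inputs assumed, because the document gives none**
- ANCOVA slope b of follow-up on baseline LVEF: 0.5 to 0.7.
- Between-arm LVEF shift d already present at the scan: derived in step 3.

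**Step 1. Reproduce the sample size.** The standardised difference is 10.8/12 = 0.9. A two-sample t-test needs 26.94, so 27 per arm or 54 in total, with power 0.901. The stated figure is correct and is not in dispute.

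**Step 2. Exposure by the end of day 5.**
- Treatment arm: 5 × 5 mg = 25 mg, of a course of 5 × 14 + 2.5 × 42 = 175 mg (14%).
- Control arm: 5 × 2.5 mg = 12.5 mg, of a course of at most 7 × 2.5 = 17.5 mg (71%).
- Difference between arms: 12.5 mg.

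**Step 3. Shift implied by the plan's own reasoning.** The statistical section assigns controls one tenth of the benefit because they receive one tenth of the cumulative dose (17.5/175 = 0.1), so it treats benefit as proportional to dose. On that logic d = 12 × 12.5/175 = 0.86 points. This is an upper value for that logic, because it takes every scan on the last permitted day and lets the 6-month benefit of each dose appear at once.

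Two other simple accruals of the 10.8 points give a similar order of size:
- linear over 6 months: 10.8 × 5/182 = 0.30;
- linear over 8 weeks: 10.8 × 5/56 = 0.96.

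**Step 4. Effect on the ANCOVA estimate.** Expected estimate ≈ 10.8 − b × d, with power from the t-test at 27 per arm and SD 12.

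| d | b | Points lost | Share of 10.8 | Expected estimate | Power |
|---|---|---|---|---|---|
| 0 | any | 0 | 0% | 10.8 | 0.901 |
| 0.86 | 0.5 | 0.43 | 4.0% | 10.37 | 0.876 |
| 0.86 | 0.7 | 0.60 | 5.6% | 10.20 | 0.865 |

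Across d from 0.30 to 0.96 with the same slopes, the loss runs from 0.15 to 0.67 points, or 1% to 6% of the target.

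**Step 5. Direction.** If bromocriptine raises LVEF early, d is positive and the estimate moves towards no difference. If the drug has no effect, it does not shift the covariate, and this mechanism cannot create a false positive.

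**The case against.** The strongest reply is that the effect is small and conservative. Both arms take bromocriptine throughout the window, so only the dose difference matters. Five days is an outer limit, actual scan times are not reported, and some scans may precede any effect. All of this stands, and it is why the size is put at about half a point.

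A reader might infer a much larger loss, for instance by supposing an early difference of 3 points, which at a slope of 0.7 removes 2.1 points or 19% of the target. The documents offer no source for such a shift; it is 3.5 times what the plan's dose logic gives. Nor should the whole shift be counted as lost, as it would be on a raw change score: the planned primary model is an ANCOVA on follow-up LVEF.

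A reader might also infer that the reported dropouts undermine the intention-to-treat analysis through missing baselines. The current-status section reports 6 dropouts after randomisation, 5 of them controls who wanted the treatment-arm regimen. It does not say that any left before the baseline scan. If they left follow-up, the missing item is the 6-month LVEF, which no change of baseline repairs. Handling of missing data can properly wait for the detailed analysis plan. Loss through a missing baseline is a possible pathway, not a demonstrated one.

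Finally, it can be said that CMR is not always possible before treatment in acute heart failure, and that outcome assessment is blinded. The first explains a late scan but does not make it a pre-treatment covariate. The second limits reading bias but does not address scan timing.

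**Conclusion.** The point holds as a flaw in the stated timing rule. The protocol positively permits a post-randomisation, post-dose value to serve as the primary endpoint's reference and as the ANCOVA covariate.

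The likely consequence is modest: about 0.4 to 0.6 points lost from 10.8, and power of about 0.87 to 0.88 instead of 0.90, biased towards no difference. These figures rest on dose-proportional benefit, scans on the last permitted day, assumed slopes of 0.5 to 0.7, and SD 12 at 27 per arm. The document supplies neither an early effect nor a slope, so the true size is unknown.

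Allocation-dependent timing or absence of the scan is a risk that the design leaves open, without evidence that it occurred. The flaw is worth correcting because the correction is cheap and the detailed analysis plan was still to be written.

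**What to change.** 1. For patients still to be enrolled, obtain the baseline CMR, or the two-echocardiogram fallback, before the first study dose wherever this does not delay treatment. With 49 of 60 enrolled by October 2014, this reaches about 11 patients.
2. For all patients, record the interval from first dose to baseline scan and report it by arm.
3. In the detailed analysis plan, pre-specify two analyses alongside the CMR-baseline model: an ANCOVA using the pre-randomisation echocardiographic LVEF as covariate for all randomised patients, and an ANCOVA with the CMR baseline restricted to pre-dose scans.

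Whether the echocardiographic value should replace CMR as the primary covariate is open to debate. It is free of treatment influence, and a covariate need not share the outcome's modality. But it is a different measurement from the CMR outcome, and its range is cut by the entry criterion, so it may explain less of the outcome variance. The recommendation does not depend on settling this.

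The cost is one date and time field, a few lines in the analysis plan, a little more analysis work, and possibly lower precision in the model with the echocardiographic covariate.

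### The primary ANCOVA omits the minimisation factors; if any is prognostic beyond baseline LVEF, the test is conservative and about 1 to 5 points of attainable power are forgone

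*Protocol article*

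**What the plan says.** Under *Enrolment and randomization (visit 1)*, the protocol article states: "A central computerized randomization (modified according to Pocock 15 and Pocock and Simon 16) of patients fulfilling the inclusion criteria is performed". The ratio is equal: "Patients are randomized in a 1:1 ratio to either the treatment group or the control group". The balancing factors are not listed.

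Under *Statistical consideration*, the method is fixed ("Regarding the primary endpoint, an analysis of covariance will be performed") and the model is then written out: "The follow-up LVEF will be defined as dependent variable, the treatment group as fixed factor and the baseline LVEF as covariate". No allocation factor is among its terms.

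The same section sizes the trial on a difference and spread given as "this will reduce the average gain in LVEF to 10.8 % in absolute terms with a standard variation of 12" points, "in a two-sided difference test with a type I error level of 0.05 and a power of 0.9", and concludes that "a total of 54 patients is needed, 27 per group". It adds that a detailed analysis plan will be written before the final analysis.

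**The concern.** Minimisation makes the arms more alike on the chosen factors than chance would. If such a factor predicts follow-up LVEF, the treatment difference varies less from one hypothetical trial to the next than under simple randomisation. A model without the factor cannot see this. The factor's variation stays in the residual, and the standard error is computed as if the arms could have differed on it by chance. The reported standard error is then too large, the confidence interval too wide and the p-value too high on average.

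Precision is at stake, not false-positive risk. With 27 evaluable patients per arm, precision that costs no extra patients is worth having.

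**Working it through.** **Inputs.** From *Statistical consideration*: difference 10.8 points, SD 12 points, two-sided alpha 0.05, power 0.9, 27 per group. From *Enrolment and randomization*: 1:1 allocation of Pocock/Pocock-Simon type. Not in the document, hence assumed: the share R² of outcome variance, beyond baseline LVEF, that the balancing factors explain. The range is 0 to 0.30.

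**Step 1: reproduce the plan's figure.** The standardised difference is 10.8/12 = 0.9. An unadjusted two-sample t-test at alpha 0.05 and power 0.9 needs 26.94, so 27 per group and 54 in total, with power 0.901. Allowing for 10% dropout, 54/0.9 = 60. The stated size therefore reproduces exactly with no variance reduction from balancing factors or from baseline LVEF.

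**Step 2: reported against true standard error.** Unadjusted, SE = 12 × √(2/27) = 3.27. With the arms perfectly balanced on the factors, the true SE is 3.27 × √(1 − R²), while a model without the factors still reports about 3.27. The actual type I error is then approximately 2 × [1 − Φ(1.96/√(1 − R²))]. The power with the factors in the model is that of a t-test with SD 12 × √(1 − R²) at 27 per group.

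| R² (assumed) | True SE | 1.96/√(1 − R²) | Type I error, stated model | Power with factors added |
|---|---|---|---|---|
| 0 | 3.27 | 1.96 | 0.050 | 0.901 |
| 0.10 | 3.10 | 2.07 | 0.039 | 0.928 |
| 0.20 | 2.92 | 2.19 | 0.028 | 0.952 |
| 0.30 | 2.73 | 2.34 | 0.019 | 0.972 |

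**Step 3: simulate the allocation.** Minimisation balances margins and does so imperfectly, so the closed form is a limit. Simulation A used 54 patients, SD 12, two assumed binary factors, marginal minimisation with a biased coin of 0.8, baseline LVEF in both models and 3,000 runs per scenario. Simulation B was a separate run on the same design: marginal minimisation, 54 patients, SD 12, two assumed binary factors.

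| R² | Type I error, stated model (A; B) | Power at 10.8, stated model (A; B) | Power at 10.8, factors added (A; B) |
|---|---|---|---|
| 0 | 0.050; 0.052 | 0.903; – | 0.901; – |
| 0.10 | 0.035; 0.043 | 0.908; 0.910 | 0.923; 0.923 |
| 0.20 | 0.036; 0.032 | 0.908; 0.918 | 0.946; 0.945 |
| 0.30 | 0.018; 0.023 | 0.931; 0.917 | 0.972; 0.965 |

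In A, the stated model reported a mean SE of about 3.29 for R² of 0.10, 0.20 and 0.30, against empirical values of about 3.1, 3.0 and 2.8. With the factors added, type I error was 0.048, 0.054 and 0.045. The scatter between A and B is of the order of simulation error: for a rate of 0.036 in 3,000 runs, √(0.036 × 0.964/3000) = 0.003.

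**Step 4: power forgone.** In A: 0.923 − 0.908 = 0.015, 0.946 − 0.908 = 0.038, 0.972 − 0.931 = 0.041. In B: 0.923 − 0.910 = 0.013, 0.945 − 0.918 = 0.027, 0.965 − 0.917 = 0.048. That is about 1 to 5 points. At R² = 0, adding the factors cost 0.903 − 0.901 = 0.002.

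**The case against.** The strongest reply is that this is a journal article condensing a full protocol. The factor list may stand there, and the model may be completed in the later analysis plan. This holds for the list: its absence is not a fault. It does not dispose of the model, which the article writes out term by term. Adding the factors would change a stated model, not fill a blank.

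A second reply is that baseline LVEF may itself be the main balancing factor, in which case it is already modelled. This is possible, and the gain would then be small. The match need not be exact, however. Eligibility rests on an echocardiographic LVEF, whereas the baseline CMR value may be obtained up to five days after bromocriptine is started. An LVEF used at allocation could therefore be a different, correlated measurement.

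A reader might infer three stronger claims that the document does not support:

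- *Power that the design relied on is being lost.* Step 1 shows otherwise. The 54 patients come from an unadjusted test, and the stated model keeps at least 0.9 in every simulated scenario.
- *The standard error is certainly too large.* With unnamed factors this is conditional. At R² = 0 the stated model is correct.
- *The loss is critical because crossover shrinks the effect.* *Current status* reports five control patients who dropped out wishing to have the treatment-arm therapy. Assuming 20% of controls crossed over gives 10.8 × 0.8 = 8.6 points and a power of about 0.74. The article does not say that these patients received that therapy, and the low power would come from the assumed dilution, not from the omitted factors.

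**Conclusion.** The point holds in conditional form. The allocation is of minimisation type and the stated primary model ignores its factors. If any factor other than baseline LVEF is prognostic, the analysis is conservative: type I error is about 0.04, 0.03 or 0.02 when the factors explain 10, 20 or 30% of outcome variance, and about 1 to 5 points of attainable power are forgone at the planned difference. These sizes rest on the assumed R² and on two assumed binary factors; the document gives neither. Planned power is met and a significant result would remain valid. This is a nearly free improvement, not a threat to the trial's conclusions.

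**What to change.** In the primary ANCOVA, regress follow-up LVEF on treatment, baseline LVEF and every minimisation factor actually used by the randomisation centre. If baseline LVEF is the only one, say so; the stated model then stands. If centre is a factor, enter it as a random effect or pool small centres by a rule set in advance, because 11 fixed centre terms are too many for 54 patients. A re-randomisation test under the actual algorithm is an optional sensitivity check.

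The detailed analysis plan was still to be written, so the change fits there. It takes a sentence or two and a few degrees of freedom, with practically no loss of power if the factors are not prognostic.
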